#### **3.1.4. Study Population**

LIFE plans to recruit sedentary and physically impaired, but ambulatory, community living older persons age 70 to 89 years. The specific inclusion and exclusion criteria are summarized below. These criteria are intended to select a population that is at higher risk of experiencing the major mobility disability outcome, would most likely benefit from the physical activity intervention, and would most likely comply with the intervention and assessment protocols. This age group is selected because it is at high risk of major mobility disability, and it may have a sufficiently long life expectancy to participate in a trial that lasts up to 3.5 years.

#### **3.2. Intentionally Blank**

### 3.3. Sample Size Considerations

The LIFE trial has targeted the recruitment of **1600 participants** across 8 Field Centers.

The **primary aim** of the LIFE Study is to assess the long-term (average 2.7 yrs) relative effect of randomization of sedentary persons aged 70 to 89 years to a physical activity intervention on the **primary outcome** of time until major mobility disability defined as inability to walk 400 m.

The primary study hypothesis of LIFE will be tested based on a two-tailed significance level of 0.05. In this analysis, the "intention to treat" approach will be used in which participants are grouped according to randomization assignment.

The main comparisons of intervention groups with respect to the distribution of time until the first post-randomization occurrence of a primary outcome will be based on survival analyses. To compare intervention arms, we will use a likelihood ratio test from a Cox regression model, stratified by field center and gender. Failure time is measured from the time of randomization.

**Incidence of the Primary Outcome:** In the LIFE Pilot study (LIFE-P), after exclusion of LIFE-P participants reporting >125 min of moderate level exercise at baseline, we estimated the 1-year failure rate in the SA arm to be 18% (Kaplan-Meier estimate). LIFE-P was not designed to estimate whether this rate increases in future years of follow-up. However, from Health ABC data we project the annual incidence rate may increase by as much as 29% in years 2-4 in participants with characteristics similar to LIFE. Using this, we have conservatively incorporated a 15% increase in the average annual incidence rate in power calculations. Thus, we adopt assumptions of an initial annual incidence rate of **18%** and project that this rate will increase, on average, to **21%** after two years of follow-up.

**Effect Size:** We have calculated the power for effect sizes ranging from 20% to 25% relative effects. While too small to estimate a relative effective size with precision, LIFE-P observed a 29% (hazard ratio=0.71; 95% CI [0.44,1.20]) relative reduction in this primary outcome. A sensitivity analysis described below was performed to examine how varying levels in the rates of drop-ins, drop-outs, and non-adherence affect our relative effect sizes.

**Average Follow-up:** We assume that recruitment will take 21 months. Power is calculated under two scenarios: 1) an assumption of a uniform recruitment rate; and 2) that the recruitment rate will accelerate during these 21 months so that approximately **50%** of participants will be recruited in the first 12 months, and **50%** will be recruited in the final **9** months. Close-out visits will occur for 3 consecutive months. The first participant recruited will have a close-out visit at 42 months (3.5 years) of follow-up and the final randomized participant will be followed for 23 months (1.9 years). Using these projected recruitment rates and lengths of follow-up, the average follow-up time will be approximately 31 months.

**Observational Follow-up:** Following the completion of the study intervention period, all participants will be asked to complete an additional assessment visit approximately one year after their last assessment visit to gather additional safety data and confirm the occurrence of the persistent mobility disability outcome. This visit will be referred as the Post Intervention Visit (PIV).

**Loss to Follow-up:** In LIFE-P, 400 m walk results or definitive adjudications were obtained in 94% (6 months) and 92% (12 months) of participants. We will assume that **loss to follow-up** accumulates at **8%/yr** throughout LIFE and factor this into all projections of power below. If loss to follow-up accrues at 7%/yr or 9%/yr rather than 8%/yr, the power for detecting the specified effect sizes would be increased or decreased by only 1%.

**Inference:** Our projections are based on a log-rank test with **2-sided significance level 0.05**. We have not adjusted this for interim analyses; however, the approach we recommend (Chapter 9) will not alter the final critical value materially.

**Calculations:** We have used SAS Proc Power, to allow incorporation of the increase in event rates during follow-up years 2-3.7 into our power calculations. In using this procedure, we assumed a uniform recruitment rate over 21 months. We have used the simulation option of NQuery Advisor to allow for calculation of power assuming recruitment of 50% of participants in the final 9 months of the 21 month recruitment period.

**Results:** Table 3.3.1. contains the power to detect relative effect sizes ranging from 20% to 25% for our total sample size of **1,600**, assuming uniform recruitment over 21 months. Using NQuery Advisor, and assuming the non-uniform recruitment schedule previously mentioned, we find that the power figures reported in Table 3.3.1 remain the same or decrease by less than 1% for any assumed effect size.

| Table 3.3.1 Power for Relative Effect Sizes |            |            |            |            |            |
|----------------------------------------------------|------------|------------|------------|------------|------------|
| 20%                                         | 21% | 22% | 23% | 24% | 25% |
| 76%                                                | 80%        | 84%        | 87%        | 90%        | 93%        |

Because of ethical concerns related to withholding the possibility of randomization to participants far along in the screening process that have been found to be eligible after the targeted sample size has been reached, LIFE will allow recruitment for up to a total of 1680 participants. This will allow each site to recruit an additional 10 participants that are in the screening “pipeline” at the time that the targeted 200 per site is reached. This recruitment would result in the power estimates in Table A should the full 1680 participants be recruited.

| Table A. Power for Relative Effect Sizes (N=1680) |            |            |            |            |            |
|----------------------------------------------------------|------------|------------|------------|------------|------------|
| 20%                                               | 21% | 22% | 23% | 24% | 25% |
| 78%                                                      | 82%        | 86%        | 89%        | 92%        | 94%        |

The **secondary aims** of the LIFE Study are to assess the relative effect of the intervention on the following **secondary outcomes**:

- Cognitive function;
- Serious fall injuries;
- Persistent mobility disability and the combined outcome of major mobility disability or death;
- Proportion of 400 m walk failures over time;
- Disability in activities of daily living; and
- Cost-effectiveness

We have also examined the power available for secondary outcomes.

The focus for assessing the relative effect of the PA intervention on cognition is based on two secondary cognitive outcomes: the Digit Symbol Substitution Test (DSST) and the Hopkins Verbal Learning Test (HVLT). Each will be tested at the 2-sided  $\alpha=0.05$  level. LIFE-P results, and data from other cognitive trials we have conducted (e.g. WHISCA, CoSTAR, GEMS), indicate that longitudinal correlations of these measures are likely to range from  $r=0.50$  to  $r=0.70$  over 4 yrs. In GEMS, at 4 yrs 92% of all expected face-to-face cognitive assessments (3MSE, CDR and ADAS-COG) were completed in a population of adults age  $\geq 75$  years (mean 79 years). In LIFE-P, retention was very strong at 12 months. Meta-analyses report that measures of executive function on average are relatively improved by 0.3 standard deviations (SD) by aerobic exercise interventions. Since most trials contributing to these meta-analyses were conducted in more healthy cohorts and are of shorter duration than LIFE, we anticipate that the effect size in LIFE will be less: we target an average effect size of half of this (e.g. 0.15 SD). We project from LIFE-P that this translates to average effects of 1.8 (DSST; and 0.8 (HVLT) units. Data

from the Women's Health Initiative Memory Study (WHIMS) indicate that annual assessments are not optimum in many cognitive trials, thus we will collect data only at baseline and year 2 (and assume an 8%/yr accumulating lost follow-up). Standard power calculations (i.e. a covariate-adjusted z-test with Bonferroni critical value of 1.96) provide the powers listed in Table 3.3.2 associated with drop-in/drop-out rates of 0%, 10% and 20% for both arms and exam times (i.e., reducing the difference between arms by these amounts).

| Table 3.3.2              | Projected Power: N=1,600 Enrolled                              |     |     |
|--------------------------|----------------------------------------------------------------|-----|-----|
|                          | Cross-Over Rates (applied equally to both arms and exam times) |     |     |
| Longitudinal Correlation | 0%                                                             | 10% | 20% |
| 0.50                     | 89%                                                            | 82% | 72% |
| 0.60                     | 93%                                                            | 87% | 79% |
| 0.70                     | 97%                                                            | 94% | 87% |

**Other Secondary Outcomes:** We have also projected the power to detect differences in other secondary outcomes. We adopt 2-sided Type 1 error of 0.05 for these outcomes. For serious fall injuries, during LIFE-P, we encountered 7 adjudicated serious falls among the N=211 SA participants and 3 serious falls among the 213 PA participants (p=0.22). The cumulative hazards (based on Kaplan-Meier plots) of falls in the SA participants were 0.032 (12 months) and 0.060 (18 months). If we conservatively project forward a 3%/yr incidence rate of new injurious falls in the SA participants and use methods similar to those described above for the primary outcome, we project we will have 80% and 90% power to detect relative hazard ratios of **1.84** and **2.05**, respectively. We expect power for disability in ADLs to be similar to what we project from the FAST Disability Score: 80% (90%) power to detect reductions in the rates of adverse changes of **67% (78%)**. Persistent mobility disability is operationally defined as failure to complete a 400 m walk at two successive 6 month exams. We have estimated and projected forward transition probabilities for persistent disability. A sample size of **n=1,600** participants is expected to allow the detection of effect sizes of **85%** and **98%** with 80% and 90% power. We expect the power for combined major mobility disorder or death to be similar to that for our primary outcome.

Additional **tertiary** aims of the LIFE trial are to explore the effects of the intervention on Mild Cognitive Impairment / Dementia (MCI/D).

We expect the **prevalence** of MCI/D in the LIFE cohort at baseline to be much less than in the community due to

| Table 3.3.3 Group | Effect Size | 2%/yr SA Incidence Rate   |       | 2.5%/yr SA Incidence Rate |       | 3%/yr SA Incidence Rate   |       |
|-------------------|-------------|---------------------------|-------|---------------------------|-------|---------------------------|-------|
|                   |             | Cumulative 2-yr New Cases | Power | Cumulative 2-yr New Cases | Power | Cumulative 2-yr New Cases | Power |
| SA                | ---         | 27                        |       | 34                        |       | 40                        |       |
| PA                | 40%         | 16                        | 33%   | 20                        | 43%   | 24                        | 48%   |
|                   | 50%         | 13                        | 55%   | 17                        | 62%   | 20                        | 70%   |
|                   | 60%         | 10                        | 75%   | 13                        | 84%   | 16                        | 88%   |

a "healthy volunteer" effect and the trial's eligibility criteria. For example, WHIMS found that only 11/7482 (0.15%) enrollees from among Women's Health Initiative trial participants met study criteria for MCI/D. The rate will likely be higher among LIFE participants, who are selected to be more physically compromised than WHIMS participants, but is difficult to predict. We adopt a baseline prevalence of 10% in our calculations of power. We apply the 8%/yr **lost to follow-up rate** adopted for other LIFE outcomes. This translates to data collection rates of 84.6% at 2 years. The **incidence** of MCI/D in RCTs and cohort studies ranges from 1-4%/yr. The LIFE cohort will be selected to be at increased risk for mobility disability, and is thus also expected to be at increased risk for cognitive decline. We use a rate of 2.5%/yr in our sample size

projections, but also examine the power for rates of 2.0%/yr and 3.0%/yr. We will explore **effect sizes** of 40-60%. Factoring in the baseline prevalence and follow-up rates we obtain the results contained in Table 3.3.3 LIFE is projected to provide **70%** statistical power to detect an effect of 50% if SA incidence is 3%/yr.

Power for combined cardiovascular events is presented in Table 3.3.4. We have assumed the same 8%/year loss to follow-up assumed by the LIFE main trial. We expect that the annual event rate is approximately 4%/year but have also calculated power for 2% and 6%/year. Using a time-to-event analysis, we will have 51% power for a 30% effect (HR of 0.7) using a two-sided test at the 5% level. Power ranges between 29 and 99% in these scenarios, depending on the background event rate and the effect size. Power for hospitalized pulmonary disorders is presented in Table 3.3.5.

Calculations were similar as for CVD event power. Because of the lower expected event rates (even with larger assumed effect sizes), the power is considerably lower. Power for ventilatory capacity is presented in Table

3.3.6. For simplicity and to be conservative, we have assumed an analysis of covariance model with adjustment for baseline but have not accounted for multiple follow-up measurements. A mixed model will ultimately be used to account for this correlation. Assumed standard deviations were 0.57 for FEV1 and 0.66 for FVC. With effect sizes of 0.05 units, there is modest power, but effect sizes of 0.1 there is substantial power. Power for sleep wake disturbances are presented in Table 3.3.7. As above, we assume 8%/year loss to follow-up. With a 5%/year event rate and a 30% effect (hazard ratio of 0.7), we would have 59% power to detect an effect using a two-sided test at the 5% level.

| Table 3.3.4. CVD Event Power |                         |                         |                         |
|------------------------------|-------------------------|-------------------------|-------------------------|
| Effect Size                  | 2%/yr SA Incidence Rate | 4%/yr SA Incidence Rate | 6%/yr SA Incidence Rate |
| 30%                          | 29%                     | 51%                     | 67%                     |
| 40%                          | 49%                     | 78%                     | 91%                     |
| 50%                          | 70%                     | 94%                     | 99%                     |

| Table 3.3.5. Hospitalized Pulm Event Power |                           |                           |                         |
|--------------------------------------------|---------------------------|---------------------------|-------------------------|
| Effect Size                                | 0.1%/yr SA Incidence Rate | 0.5%/yr SA Incidence Rate | 1%/yr SA Incidence Rate |
| 40%                                        | 7%                        | 16%                       | 28%                     |
| 50%                                        | 9%                        | 24%                       | 42%                     |
| 60%                                        | 11%                       | 34%                       | 59%                     |

| Table 3.3.6 Ventilatory Capacity Power |             |      |     |
|----------------------------------------|-------------|------|-----|
| Correlation                            | Effect Size | FEV1 | FVC |
| 0.3                                    | 0.05        | 45%  | 36% |
|                                        | 0.1         | 96%  | 89% |
| 0.5                                    | 0.05        | 53%  | 42% |
|                                        | 0.1         | 98%  | 94% |
| 0.7                                    | 0.05        | 69%  | 56% |
|                                        | 0.1         | >99% | 99% |

| Table 3.3.7. Sleep-wake disturbance Power |                         |                         |                         |
|-------------------------------------------|-------------------------|-------------------------|-------------------------|
| Effect Size                               | 3%/yr SA Incidence Rate | 5%/yr SA Incidence Rate | 7%/yr SA Incidence Rate |
| 20%                                       | 20%                     | 30%                     | 39%                     |
| 30%                                       | 40%                     | 59%                     | 73%                     |
| 40%                                       | 66%                     | 86%                     | 95%                     |

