#### **6.2.18. Ventilatory Capacity**

Ventilatory capacity will be assessed by spirometry and maximal inspiratory pressure (MIP). Spirometry will be recorded by the EasyOne™ PLUS spirometer to record average FEV6 and FEV1 over three reproducible trials. MIP will be recorded by a pressure gauge fitted with a disposable cardboard mouthpiece. The assessment of MIP will allow us to evaluate respiratory muscle weakness as a cause of reduced ventilatory capacity and as a risk factor for subsequent hospitalization (e.g. pneumonia). Older persons who have impaired skeletal muscle function may also have respiratory muscle weakness. Ventilatory capacity will be assessed at SV2 and at the 6, 18 and 30 month clinic visits.

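### Tables 3.3.3 and 3.3.6 lack losses that Section 3.3 says were applied, and Table 3.3.2 defines its cross-over rates in two incompatible ways

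*Protocol*

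**What the plan says.** All of this is in Protocol Section 3.3 unless noted.

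- **Loss to follow-up.** Loss is taken to accumulate at 8% per year "throughout LIFE and factor this into all projections of power below".
- **Table 3.3.2 (DSST and HVLT, secondary outcomes).** The table is headed "Projected Power: N=1,600 Enrolled". It uses an effect of 0.15 SD, longitudinal correlations of 0.50 to 0.70, a year-2 measurement and a "covariate-adjusted z-test with Bonferroni critical value of 1.96". The text gives powers "associated with drop-in/drop-out rates of 0%, 10% and 20% for both arms and exam times (i.e., reducing the difference between arms by these amounts", and the column heading reads "Cross-Over Rates (applied equally to both arms and exam times". Each outcome is tested at two-sided 0.05, here and in Section 12.2.
- **Table 3.3.3 (MCI/dementia, tertiary).** The text adopts 10% baseline prevalence and 84.6% data collection at two years, then states: "Factoring in the baseline prevalence and follow-up rates we obtain the results contained in Table 3.3.3". It highlights 70% power for a 50% effect at 3% per year.
- **Table 3.3.6 (ventilatory capacity, tertiary).** The SDs are 0.57 (FEV1) and 0.66 (FVC). The method is introduced thus: "For simplicity and to be conservative, we have assumed an analysis of covariance model with adjustment for baseline". The sentence goes on to say that multiple follow-up measurements were not accounted for. No exemption from the 8% loss is stated.
- **What is measured.** Section 6.2.18 says spirometry is used "to record average FEV6 and FEV1 over three reproducible trials", at baseline and at 6, 18 and 30 months. Section 12.2 (Tertiary Aim #5) analyses FVC and FEV1.

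**The concern.** A power table is useful only if the assumptions stated beside it are the ones used to compute it. In two tables a stated reduction in sample size appears to be absent. In the third, the same percentage is described both as a rate in each arm and as the total reduction of the difference, and these differ by a factor of two.

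What is at stake is how the secondary and tertiary results are read. A reader of Table 3.3.2 could believe that cognitive power stays above 70% when a fifth of each arm crosses over. A reader of the other two tables would credit them with allowances for attrition or prevalent cases that the numbers do not contain. The primary outcome has its own calculation and is not involved.

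**Working it through.** **Common inputs.** There are 1,600 enrolled, allocated 1:1, so 800 per arm. With 8% annual loss, retention at two years is 0.92² = 0.846, so n = 677 per arm. At 30 months, 800 × 0.92^2.5 ≈ 650. At 6 months, 800 × 0.92^0.5 ≈ 767.

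**Table 3.3.2.** Power = Φ(0.15k / √(2(1−r²)/n) − 1.96), with n = 677 and k the fraction of the difference that remains. For r = 0.50 and k = 1, the standard error is 0.866 × √(2/677) = 0.0471, and 0.15/0.0471 − 1.96 = 1.23, which gives 89%.

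| r | k=1 | k=0.9 | k=0.8 | Printed (0/10/20%) | k=0.6 |
|---|---|---|---|---|---|
| 0.50 | 89.0 | 81.8 | 72.2 | 89/82/72 | 48 |
| 0.60 | 93.2 | 87.4 | 78.8 | 93/87/79 | 54 |
| 0.70 | 97.2 | 93.5 | 87.1 | 97/94/87 | 64 |

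All nine cells reproduce with attrition included and k = 1, 0.9, 0.8. If a fraction c of *each* arm crosses over, the arm means move towards each other from both sides and k = (1 − c) − c = 1 − 2c. So 10% in each arm is k = 0.8 (72/79/87%), and 20% in each arm is k = 0.6 (48/54/64%).

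**Table 3.3.3, counts.** SA cases are n × two-year incidence (0.04, 0.05, 0.06).

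- 677 per arm (no prevalent cases removed): 27.1/33.9/40.6.
- 672 per arm (84% retention, that is 1 − 2 × 0.08): 26.9/33.6/40.3.
- 609 per arm (800 × 0.90 × 0.846): 24.4/30.5/36.5.
- Printed: 27/34/40.

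**Table 3.3.3, power.** With a continuity-corrected two-proportion test, power = Φ{[(p₁−p₂) − 1/n − 1.96√(2p̄(1−p̄)/n)] / √([p₁(1−p₁)+p₂(1−p₂)]/n)}. Example at n = 609, p₁ = 0.06, p₂ = 0.03: (0.0284 − 0.0233)/0.0118 = 0.43, which gives 67%.

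| SA rate | Printed (40/50/60% effect) | Printed counts, n=677, corrected test | n=609, corrected test | n=609, uncorrected pooled test |
|---|---|---|---|---|
| 2%/yr | 33/55/75 | 34/55/76 | 30/47/66 | 35/53/72 |
| 2.5%/yr | 43/62/84 | 44/63/84 | 37/57/77 | 43/63/81 |
| 3%/yr | 48/70/88 | 48/71/88 | 45/67/85 | 50/71/88 |

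The printed counts with the corrected test give all nine printed powers within 1.1 points. Part of the gap to the fourth column comes from rounding the printed counts. With unrounded rates the corrected test at 677 gives 33/52/71, 41/62/82 and 49/72/89, so removing prevalent cases alone costs about 3 to 5 points.

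**Table 3.3.6.** Power = Φ(d / (SD·√(1−r²)·√(2/n)) − 1.96). For FEV1, r = 0.3, d = 0.05, n = 800: 0.57 × √0.91 × 0.05 = 0.0272, and 0.05/0.0272 − 1.96 = −0.12, which gives 45%.

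| r (d=0.05, FEV1/FVC) | Printed | n=800 | n=677 (2 yr) | n=650 (30 mo) |
|---|---|---|---|---|
| 0.3 | 45/36 | 45.2/35.5 | 39/31 | 38/30 |
| 0.5 | 53/42 | 52.6/41.7 | 46/36 | 45/35 |
| 0.7 | 69/56 | 69.0/56.4 | 62/50 | 60/48 |

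The rows for d = 0.1 also reproduce at 800. At 677 they become 92/83, 96/90 and >99/97, against 96/89, 98/94 and >99/99 printed.

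**The case against.** **Table 3.3.2.** A reader might infer that this table leaves out dilution or attrition. It does not: both are in the cells, and the reduction applied is exactly the one its parenthesis defines. Only the contradiction with the per-arm wording stands. A reader might also infer from the word Bonferroni that the critical value should be 2.24, which would give 83/89/95% in the 0% column. That describes a test the protocol does not plan. Each outcome is tested at 0.05, so 1.96 is correct and the word is stray.

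**Table 3.3.3.** The size of the power overstatement is not fixed. An uncorrected pooled test at 609 per arm comes within about 3 points of every printed cell and meets the headline 70%. A person-time variant with prevalence removed (720 × 0.92 × two-year incidence = 26.5/33.1/39.7) also lands near the printed counts, but it does not use the 84.6% two-year follow-up the text describes. Section 10.3.6 already concedes that power for this outcome may be insufficient. The mismatch between the counts and the stated inputs stands under any test.

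**Table 3.3.6.** A reader might infer that calling the method conservative is false. That wording concerns ignoring repeated measurements, and on that it is fair. Suppose a common within-person correlation, a constant effect and 650 per arm at all three visits. The adjusted variance factor is then (1+2r)/3 − r² instead of 1 − r², and FEV1 power for d = 0.05 is about 66% at r = 0.3 and 81% at r = 0.7, above the printed 45% and 69%. So the documents do not show that power for the planned mixed model is overstated. The table is still said to contain a loss that it does not contain.

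**Conclusion.** The point holds as an inconsistency between stated inputs and printed figures.

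- **Table 3.3.3** does not remove the 10% prevalent cases. The counts should be about 24/30/37. The quoted 70% becomes about 67% with the test that reproduces the table and about 71% with an uncorrected pooled test.
- **Table 3.3.6** contains no attrition. For d = 0.05 the shown analysis loses 5 to 7 points at two-year retention and up to 9 at 30 months. At the 6-month visit the loss is small (FEV1 44% against 45% at r = 0.3).
- **Table 3.3.2** is correct for total dilution of 0, 10 and 20%, and wrong if its columns are read as rates in each arm.
- **FVC** appears in the power table and the analysis plan, while the measurement section lists FEV6. This is a naming conflict, not a power error.

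These results assume 1:1 allocation, compounding 8% annual loss and normal-approximation tests. Tables 3.3.3 and 3.3.6 concern tertiary outcomes and Table 3.3.2 secondary ones. Nothing here touches primary power.

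**What to change.** 1. Reprint Table 3.3.3 with 609 at risk per arm and name the test used.
2. Reprint Table 3.3.6 with 8% annual loss at a stated visit. If credit is wanted for repeated measures, state the assumed correlation structure and compute it.
3. Relabel the Table 3.3.2 columns as total dilution of the difference and drop the per-arm wording, or keep the per-arm wording and recompute with 1 − 2c.
4. Delete the word Bonferroni.
5. Reconcile FVC (Section 3.3 and Tertiary Aim #5 in Section 12.2) with FEV6 (Section 6.2.18), so that the measured, powered and analysed variables agree.

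The cost is editorial: somewhat less favourable power figures for tertiary outcomes, and no change to sample size, conduct or the primary analysis.
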